#### Data analysis

A descriptive analysis by preterm birth will be carried out calculating means and medians for quantitative variables and proportions for categorical variables. T-test or Mann-Whitney test and Pearson Chi-squared or Fisher test will be used for comparing among exposure and outcomes groups per pregnancy. A multivariate logistic regression will be fitted to control for possible confounders. Relative risks and 95% confidence interval will be calculated for the outcomes.

For fetal and neonatal outcomes, multilevel models will be used to analyse continuous outcomes and generalized estimating equations will be used to assess categorical outcomes to adjust for the clustering of twins in mothers. A secondary analysis of length of gestation after fetoscopy will be plotted on a staggered-entry Kaplan-Meier curve where gestational age at birth (in days) will be the final event. Elective A Mantel-Cox test will be performed to test statistically for significant differences in the time interval between fetoscopy and birth. All analyses will be carried out with SPSS® 19.0 statistical package (IBM Company SPSS Inc. Headquarters, Chicago, Illinois. USA). Statistical significance will be accepted in all cases with a *p* < 0.05.

We do not expect to have lost data because this study has a short follow-up time. We will also perform a per-protocol analysis.

We also intend to perform a subgroup analysis according the cervical length: over 25 mm, 15 to 25 mm and less than 15 mm. We decided to perform the subgroup analysis with these cut-off lengths because 25 mm is around the 5th centile for cervical length for twins less than 22 weeks’ gestation [24] and some groups perform cervical cerclage in TTTS patients with CL below 15 mm [13].

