## Background

Fetoscopic LASER coagulation of placental anastomoses (FLC) with or without Solomon technique [1] is the treatment of choice for severe Twin-to-Twin Transfusion Syndrome (TTTS) [2]. This procedure completely changed the natural history of TTTS [3]. However, although this first and most important step was taken and survival rates and neurological outcomes improved, premature births remain a serious concern: 41% of patients will deliver before 32 completed weeks [4]. Therefore, an effort to reduce prematurity is required. Cervical pessary placement could constitute an option to reduce prematurity, regardless of cervical length at the time of fetoscopy.

Transvaginal ultrasound permits the identification of twin pregnancies at high risk of preterm delivery [5, 6]. It is known that cervical length (CL) plays a role in the onset of preterm birth. The pathophysiology of premature ripening of the cervix varies between singleton and multiple pregnancies with twin pregnancies having a higher prevalence of short cervix at 23 weeks [7]. Regarding TTTS, Yamamoto et al. showed that short CL before treatment is an independent risk factor for preterm delivery [8].

The prematurity rate in cases of severe TTTS in patients with long cervix treated by FLC remains very high [9–11]. Although many cases are delivered prematurely for medical indications (mainly selective intrauterine growth restriction), a large proportion will also develop spontaneous preterm labour [12].

Information is lacking regarding the best therapeutic option in patients with short cervix who also require fetoscopy [9–11]. Salomon et al. suggested the use of an emergency cerclage in cases of TTTS with a short cervix at the time of surgery [13]. In this observational study, the emergency cerclage could prolong pregnancy and improve perinatal outcomes. It was the first study to demonstrate a potential benefit to prevent premature delivery in such cases. Nevertheless, emergency cerclage continues to be an invasive procedure requiring anaesthesia. It also bears the risk of infection, local inflammatory reactions and premature rupture of membranes, although these were not observed in the Salomon study [14–16]. In current practice an emergency cerclage is usually performed for a cervical length less or equal to 15 mm after fetoscopic surgery in cases of TTTS, although the benefit of the cerclage in these cases has been recently questioned [17].

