## Methods/design

### Aims

We will perform a randomised trial (the PECEP LASER Trial: Arabin Cervical Pessary for prevention of preterm birth in cases of Twin-to-Twin Transfusion Syndrome treated by Fetoscopic Laser coagulation) to assess the effect of the Arabin cervical pessary on the rate of preterm delivery in cases of monochorionic pregnancies with twin-twin transfusion syndrome requiring fetal therapy.

This is a multicenter study to be conducted in the Hospital Universitari Vall d’Hebron in Barcelona (Catalunya, Spain), the Universitaire Ziekenhuizen in Leuven (Belgium), and the University Medical Centrer Hamburg-Eppendorf (UKE) in Hamburg (Germany). All centers have approval from the respective Medical Ethics Committees to conduct the trial.

The trial was registered in ClinicalTrials.gov in December 4th, 2011 (https://www.clinicaltrials.gov/ct2/show/NCT01334489?term=NCT01334489&recrs=a&rank=1). The trial identifier is NCT01334489.

The study is open for other centres who wish to participate.

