### Procedures, recruitment, randomisation and collection of data

The Fetal Medicine Teams in the participating centres will counsel all women being referred for suspected TTTS. When fetoscopic LASER is planned, one of the Fetal Medicine specialists will confirm that the patient fulfils the inclusion criteria, and the study will be proposed. The patients will be informed about the intended therapeutic effect and possible side effects. The patient will be given an information sheet and if possible, she will have 24 h time to reflect on participation. If they agree, after obtaining their informed consent, they will be randomised in two groups: Usual management or cervical pessary placement.

The randomisation will be computed on-line at the platform for electronic data management based at the Catalan Institute of Pharmacology (ICF) where all data will be collected in a worldwide accessible online database. Each centre will have its own randomisation list and randomisation will be 1:1 for pessary placement versus control. Only a participant identification number in the electronic database will identify the participants. All documents will be stored securely and only accessible by trial staff and authorized personnel.

The study is not blinded.

Baseline characteristics of the women, the pregnancies and issues on the TTTS and the surgery will be recorded. The cervical length will be recorded before and after surgery and every 4 weeks until delivery. We will also record complications of the surgery, complications by the pessary and perinatal results.

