### Outcomes

The primary outcome will be delivery before 32 completed weeks.

Secondary outcomes will be related to the delivery and perinatal results: preterm delivery before 28, 30, 34 and 37 weeks; preterm rupture of membranes; hospitalisation for threatened preterm labour (including the need of tocolysis and fetal lung maturation); fetal or neonatal death; composite neonatal morbidity (any of intraventricular haemorrhage, necrotising enterocolitis, retinopathy of prematurity, proven or suspected sepsis, need of Neonatal Intensive Care, need of ventilation, phototherapy, antibiotics or blood transfusion). We will also record significant maternal adverse effects, mainly due to the pessary.

A long-term follow-up of the babies is not planned.

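### No analysis is designated as primary, and none of those listed uses centre or baseline cervical length, although both are available at no cost

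*Protocol article*

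**What the plan says.** The primary endpoint is binary: "The primary outcome will be delivery before 32 completed weeks". Women are randomised after surgery (Abstract, Methods), and on allocation the protocol article states: "Each centre will have its own randomisation list and randomisation will be 1:1 for pessary placement versus control". That is stratification by centre, though the word is not used. Three centres are named in the Aims section, which adds: "The study is open for other centres who wish to participate".

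The Background reports that "short CL before treatment is an independent risk factor for preterm delivery". The procedures section has cervical length recorded before and after surgery and every four weeks thereafter.

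For analysis, the Data analysis section says "T-test or Mann-Whitney test and Pearson Chi-squared or Fisher test will be used for comparing among exposure and outcomes groups per pregnancy". It continues: "A multivariate logistic regression will be fitted to control for possible confounders". Relative risks with 95% confidence intervals are to be calculated for the outcomes, without saying whether they are crude or adjusted. Cervical length enters only as a three-level subgroup variable. Centre is not mentioned.

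**The concern.** Three kinds of analysis are listed for the same endpoint, and none is ranked. The study is not blinded, and the Interim analysis section sets p-value thresholds (below 0.0001 after 100 women, below 0.004 after 200) without saying which test supplies the p-value. With the covariates unnamed, the text permits more than one answer to the main question.

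The rationale is also borrowed from observational work. In a randomised comparison, baseline variables belong in the model because they predict outcome or because allocation was stratified on them, not because they may confound. The trial has one variable of each kind, centre and cervical length, and commits neither to the analysis. What is at stake is some power and a clear primary result, not validity.

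**Working it through.** **Inputs from the protocol article.** Event rates 40% and 26%; power 80%; alpha 5%, or 0.045 after allowing for interim analyses; 176 or 182 per arm; drop-out 10% (Expected sample size). Three named centres (Aims).

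**Assumed, because the documents give no figures.** Control rates by centre, and the strength of cervical length as a predictor. Both are shown as ranges.

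**1. The plan's own figures.** Two proportions, pooled variance under the null, two-sided, no continuity correction:

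n = [z_α √(2p̄(1−p̄)) + z_β √(p₁(1−p₁) + p₂(1−p₂))]² / (p₁−p₂)²

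with p̄ = 0.33, √0.4422 = 0.6650, √0.4324 = 0.6576 and z_β = 0.8416.

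- Level 0.05: (1.960 × 0.6650 + 0.8416 × 0.6576)² / 0.0196 = 175.9, so 176 per arm.
- Level 0.045: (2.005 × 0.6650 + 0.8416 × 0.6576)² / 0.0196 = 181.6, so 182 per arm.

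Both match the plan exactly, so the sizing rests on an unadjusted comparison. They match only without drop-out inflation (176/0.9 gives 196 and 182/0.9 gives 203), so a 10% loss would come out of the power.

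**2. Cost of a 10% drop-out.** 0.9 × 182 = 163.8, or 164 per arm. Power at level 0.045 falls from 80.1% to 75.8%, a loss of about 4.3 points.

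**3. Centre alone.** Simulation of 400,000 trials per row: three equal centres, 182 per arm, level 0.045, common odds ratio, overall rates held at 40% and 26%. The pooled chi-squared test is compared with the centre-stratified Cochran-Mantel-Haenszel (CMH) test.

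| Assumed control rates by centre | Power, pooled | Power, CMH | Type I error, pooled | Type I error, CMH |
|---|---|---|---|---|
| 40/40/40% | 80.3% | 80.2% | 4.75% | 4.70% |
| 35/40/45% | 80.4% | 80.4% | 4.66% | 4.65% |
| 30/40/50% | 80.5% | 81.2% | 4.49% | 4.57% |
| 25/40/55% | 81.0% | 82.5% | 4.02% | 4.41% |
| 20/40/60% | 81.5% | 84.1% | 3.53% | 4.52% |

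The gain is about 0 to 0.7 points for spreads up to ±10 points, 1.5 at ±15 and 2.6 at ±20. With no centre differences, both tests sit slightly above 4.5%, so that small excess is not caused by ignoring centre. As centres diverge, the pooled test's error rate falls.

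**4. Adding cervical length.** Two simulations, 3,000 trials per setting, logistic model against the unadjusted test; b is the assumed log-odds effect per SD.

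- 182 per arm, level 0.045, adjusting for centre and cervical length: 79.9% to 82.2% at b = 0.5 (+2.3); 80.0% to 83.6% at 0.7 (+3.6); 80.0% to 86.5% at 1.0 (+6.5). Centre alone added 0.1 to 0.3 points in these runs.
- 158 per arm, level 0.05, one predictor: 74.8% to 74.7% at b = 0; 77.0% to 77.1% at 0.3; 74.9% to 76.8% at 0.5; 75.4% to 80.1% at 0.8; 75.6% to 82.7% at 1.0.

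A power of 80% from 3,000 trials has a standard error of √(0.8 × 0.2/3000) = 0.7 points, so tenths should not be over-read. The two sets agree: about 0 at b up to 0.3, about +2 at 0.5, and about +6 to +7 at 1.0.

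**5. Against the drop-out loss of 4.3 points.** At b = 0.5 about half is recovered (2.3/4.3), at 0.7 most (3.6/4.3), at 1.0 all, and at 0 to 0.3 almost none.

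**The case against.** The strongest reply is that this is a condensed article with no SAP shown, and that a covariate list and a centre term normally belong in the SAP. That stands: their absence here is not an error. An unadjusted chi-squared test also agrees with the sizing formula, and ignoring centre does not inflate the type I error. Cervical length is not overlooked either, since subgroups with cut-offs are specified.

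A reader might infer three stronger charges, and the documents support none of them.

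- *That the primary test is stated and ignores centre.* No test is labelled primary. The lack of a designation is the point.
- *That covariates will be chosen after looking at associations with outcome.* No selection procedure is described. The open wording permits this but does not plan it.
- *That odds ratios will be passed off as relative risks.* At the planned rates the two do differ: 0.26/0.40 = 0.65 against (0.26/0.74)/(0.40/0.60) = 0.53. But the text promises relative risks and never presents an odds ratio as one, and a logistic model can yield a relative risk by standardisation.

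Post-operative cervical length is a tempting covariate, but the article does not say that this measurement precedes randomisation. The pre-surgery value must, because women are randomised after surgery, and it is the measurement the Background describes as a risk factor.

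**Conclusion.** The point holds as a free improvement, not as a flaw in validity. The plan lists several analyses of delivery before 32 weeks without ranking them, and commits neither the factor that defines the randomisation lists nor the baseline predictor it names itself.

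The size is modest and conditional: about 0 to 0.7 power points from centre under moderate centre differences (2.6 in the extreme case simulated), and about 0 to 6 points once cervical length is added, over an assumed effect of 0 to 1.0 log-odds per SD. That recovers anything from none to all of the roughly 4 points a 10% drop-out would cost. Naming the primary analysis is worthwhile even at the bottom of that range.

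The gains were computed with CMH tests and logistic models. I take those for an adjusted relative risk to be similar, but this was not simulated separately.

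**What to change.** Designate one primary analysis of delivery before 32 weeks: an adjusted relative risk with 95% confidence interval, from modified Poisson regression with robust standard errors or from logistic regression with standardisation. Fix the covariates as centre and pre-surgery cervical length (continuous). Keep the centre-stratified Mantel-Haenszel relative risk as the simple check. Replace the phrase about possible confounders with this covariate list. State that the p-value from the primary analysis is the one compared with the threshold at each look. As other centres may join, say beforehand how very small centres will be combined.

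The cost is wording only. Centre is known from the randomisation list and cervical length is already recorded before surgery, so nothing changes in recruitment, data collection or sample size. If a SAP already contains these choices, it is enough to align the protocol text with it.

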### Participants

All women presenting with a monochorionic-diamniotic pregnancy with severe twin-twin transfusion syndrome between 16 and 26 weeks are eligible for the study with the exception of pregnancies complicated by major congenital abnormalities, uterine malformations, placenta praevia, active vaginal bleeding or spontaneous rupture of membranes at the time of randomization. Also patients with contraindication for pessary placement as painful regular uterine contractions, or a cervical cerclage in place will be excluded [20], as well as cases of demise of both twins after surgery.

Gestational age will be determined through menstrual history and first trimester scan.

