### Statistics

#### Expected sample size

We based our sample size calculations on the assumption that the pessary reduces the primary outcome (preterm birth <32 weeks) from 40% in the control group to 26% in the pessary group [18]. With a study power of 80% and an alpha error of 5%, (assuming an effect size of 0.5 (moderate) and expecting a potential drop out rate of 10%), the required sample size has been estimated to be 352 patients, 176 cases in each arm of the study. We will perform 2 interim analyses, so the *p*-value would be set at 0.045 (O’Brien-Fleming rule) [23] instead of 0.05 and we would therefore need to recruit 182 patients in each arm.

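### The time-to-birth curve is drawn on gestational age with staggered entry, but its Mantel-Cox test is specified on the interval from fetoscopy, so the p-value does not test the difference the curve shows

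*Protocol article*

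**What the plan says.** The Data analysis section of the protocol article announces one analysis: "A secondary analysis of length of gestation after fetoscopy". It is to be "plotted on a staggered-entry Kaplan-Meier curve where gestational age at birth (in days) will be the final event". The test that follows is a Mantel-Cox (log-rank) test, described thus: "test will be performed to test statistically for significant differences in the time interval between fetoscopy and birth". No sentence places that test on the gestational-age axis, and none stratifies or adjusts it for gestational age at fetoscopy.

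Under Participants, women with "severe twin-twin transfusion syndrome between 16 and 26 weeks are eligible", so age at entry can differ by 10 weeks. The Discussion says that most of these twins are electively delivered around 34 weeks. In the text at hand, a lone word about elective births stands just before the test sentence, and the rest of that statement cannot be read.

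**The concern.** Staggered entry on a gestational-age axis means that a woman joins the risk set at her gestational age at fetoscopy. She is then compared only with women still pregnant at the same gestational age. On the interval axis every woman starts at day 0 and is compared with women the same number of days after surgery, whatever their gestational age. These are two different log-rank tests.

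A reader who sees a curve on one axis and a p-value beside it will take the p-value to be a test of that curve. Here it would not be. The two could give different impressions, and the interval test may also be the less sensitive one. What is at stake is the interpretation and efficiency of a secondary analysis that uses the whole length of gestation, not the primary comparison.

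**Working it through.** **1. The two risk sets.** Let e be gestational age at fetoscopy and b gestational age at birth, in days.
- Curve: at gestational age t, the women at risk are those with e < t ≤ b.
- Test as worded: at u days after fetoscopy, the women at risk are those with b − e ≥ u.

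The eligibility window runs from 16 × 7 = 112 to 26 × 7 = 182 days, a spread of up to 70 days. At u = 56 days, a woman treated at 16 weeks is at 24 weeks and one treated at 26 weeks is at 34 weeks. The interval test puts them in one risk set, but the curve never compares them at those two ages. Conversely, a birth at 32 weeks falls at 32 − 26 = 6 weeks on the interval clock for one woman and at 32 − 16 = 16 weeks for the other.

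**2. The article's own figure.** No power is given for this test. The primary calculation is reproduced only to anchor the simulation. The article assumes a fall "from 40% in the control group to 26% in the pessary group" and reports that "the required sample size has been estimated to be 352 patients, 176 cases in each arm of the study". With pooled variance, two-sided, p̄ = 0.33:
- n = [z(α/2)·√(2 × 0.33 × 0.67) + z(β)·√(0.40 × 0.60 + 0.26 × 0.74)]² / 0.14²
- α = 0.05: (1.960 × 0.6650 + 0.8416 × 0.6576)² / 0.0196 = 175.9, so 176 per arm.
- α = 0.045: (2.005 × 0.6650 + 0.8416 × 0.6576)² / 0.0196 = 181.6, so 182 per arm.

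Both agree with the article (without any allowance for drop-out). Neither bears on the mismatch of clocks.

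**3. What the mismatch could cost.** Statistic on each clock: Z = Σ(d₁ − d·n₁/n) / √ΣV, two-sided 0.05, with the risk sets from step 1.
- From the article: 352 women, 1:1, entry window 16-26 weeks, 40% and 26% delivered before 32 weeks. With a single common risk the implied hazard ratio would be ln(0.74)/ln(0.60) = 0.59; the calibrated values were about 0.57-0.59.
- Assumed: uniform entry; hazard shape; planned birth at about 34 weeks (SD 7 days) or 37 weeks (SD 3 days). Cumulative hazard to day 224 is λ[112^s − (e − 112)^s] when risk follows gestational age, and λ(224 − e)^s when it follows time since surgery. A flat hazard is s = 1.

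Power in %, gestational age with delayed entry / interval, from 2000 simulated trials per row; losses in points, computed before rounding:

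| Hazard | Planned birth | Every birth an event | Loss | Planned births censored | Loss |
|---|---|---|---|---|---|
| Rising with gestational age, s = 3 | 34 wk | 60.1 / 37.6 | 22.6 | 91.5 / 88.6 | 2.9 |
| Same | 37 wk | 88.3 / 65.8 | 22.5 | 96.7 / 95.5 | 1.2 |
| Rising with gestational age, s = 5 | 34 wk | 71.3 / 35.9 | 35.5 | 95.0 / 89.8 | 5.2 |
| Same | 37 wk | 98.3 / 74.6 | 23.7 | 99.4 / 96.7 | 2.8 |
| Flat | 34 wk | 52.6 / 49.2 | 3.5 | 86.5 / 86.8 | −0.3 |
| Flat | 37 wk | 66.2 / 61.2 | 5.1 | 91.9 / 91.9 | 0.0 |
| Time since surgery, s = 2 | 34 wk | 57.7 / 59.0 | −1.4 | 89.7 / 91.8 | −2.1 |
| Same | 37 wk | 83.9 / 82.5 | 1.5 | 96.1 / 97.6 | −1.5 |

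**4. Sensitivity.** With 364 women the pattern was the same; the largest loss was 76.7 − 37.9 = 38.8 points (s = 5, planned birth at 34 weeks, every birth an event). Entry that was normal (mean 20.5, SD 2.5 weeks; 400 runs, so noisier) gave losses of 17-35 points in the four rising-hazard, every-birth-an-event settings. In the flat-hazard, every-birth-an-event settings it gave 2-10.

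A steeper Weibull hazard in gestational age (shape 9, scale 34.6 weeks; 364 women; hazard ratio 0.65) gave 94% against 64% with a 37-week cap and every birth an event. With births at the cap censored it gave 95% against 90%. With planned births at about 34 weeks it gave 65% against 34% as events and 87% against 82% censored. Other runs of this model with censoring lost 3-10 points.

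**5. Validity.** With no treatment effect, both tests rejected in about 3-6% of simulated trials.

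**The case against.** The best defence is that the analysis is introduced as one of the length of gestation after fetoscopy, and a test of the fetoscopy-to-birth interval answers that question. That stands as far as it goes: the interval is a legitimate quantity. But then the curve is on the wrong axis, and the mismatch remains. A looser reading takes the interval to be each woman's time at risk on the staggered-entry curve. It is possible, but it is not what the sentence says. Nor is this a detail simply left to an unseen analysis plan, since the article states both axes.

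The defence is stronger on size. A reader might infer that the interval test loses much of its power whatever happens. The article does not support that: it gives no hazard, and its rule for elective births is unreadable. The large losses need both a rising gestational-age hazard and every birth counted as an event. The simulations with a rising hazard also make the effect proportional on the gestational-age scale, which favours that test. In the other direction, the article's event is birth without restriction, and its Discussion keeps iatrogenic births in the intention-to-treat comparison. The high-loss setting is therefore plausible, though not established.

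Two further inferences fail. That this test might contradict the primary result was not measured; comparing two log-rank tests with each other says nothing about delivery before 32 weeks. Starting the clock at fetoscopy although randomisation follows surgery is immaterial: the pessary is inserted within 72 h of surgery, against intervals of weeks to months.

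**Conclusion.** The fault is one of specification: read literally, the curve and its test use different time scales and risk sets, so the p-value does not test the plotted difference. This follows from the text and needs no simulation. The interval test is valid under randomisation, so the issue is interpretation and power.

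The power loss is conditional. It is roughly 20-35 points (17-39 across the calibrated runs) if risk rises with gestational age and every birth is an event. It is about 1-10 points if planned or undelivered births are censored, and close to none if the hazard is flat or follows time since surgery. These figures rest on assumed entry distributions, hazard shapes and timing of planned births. The analysis is secondary, and the primary outcome, its test and the sample size are untouched.

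**What to change.** Put the test on the axis that is already plotted: a log-rank test, or a Cox model, with gestational age in days as the time scale and delayed entry at gestational age at fetoscopy or randomisation. If the interval is the quantity wanted, stratify or adjust its test for gestational age at fetoscopy and make clear that it is not the test of the gestational-age curve. In either case, complete the sentence on elective births so that it says whether they are events or are censored, because the power depends heavily on that choice.

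The cost is a sentence or two in Data analysis, with no new data. The one practical check is whether the named SPSS 19.0 can run the delayed-entry test; if it cannot, name software that can.

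### One sentence accepts significance at p < 0.05 for every test: it leaves nine secondary comparisons without family-wise control and contradicts the 0.045 level set for the primary outcome

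*Protocol article*

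**What the plan says.** All of the following is in the protocol article.

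- **Outcomes** names one primary: "The primary outcome will be delivery before 32 completed weeks".
- The same section lists eight secondary outcomes. Four are further gestational-age limits: "preterm delivery before 28, 30, 34 and 37 weeks; preterm rupture of membranes" gives these and the fifth outcome. The sixth is hospitalisation for threatened preterm labour. The last two are "fetal or neonatal death; composite neonatal morbidity". Maternal adverse effects are recorded as well.
- **Data analysis** adds a ninth secondary comparison: "A Mantel-Cox test will be performed to test statistically for significant differences in the time interval between fetoscopy and birth".
- **Data analysis** then gives one rule for all tests: "Statistical significance will be accepted in all cases with a" p < 0.05. It also plans interval estimates: "Relative risks and 95% confidence interval will be calculated for the outcomes".
- **Expected sample size** says that, because of two interim looks, the p-value "would be set at 0.045" in place of 0.05.

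Neither Outcomes nor any part of Statistics orders the secondary tests, ties them to the primary result, divides alpha among them or describes them as supportive. The 0.045 level and the stopping limits under Interim analysis deal with repeated looks, not with multiple outcomes.

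**The concern.** The article fixes a decision rule here, so this is more than detail left to an analysis plan. An analysis plan that called the secondary outcomes exploratory would contradict the sentence as it stands.

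The four extra cut-offs matter most. They split the same variable as the primary outcome at neighbouring points, while the aim in the Background is worded as reducing preterm delivery with no gestational-age limit. A trial that misses at 32 weeks could, under the rule, report a significant effect at 28, 30, 34 or 37 weeks and have it read as meeting that aim.

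The article itself shows how such results get read. The Background reports an earlier pessary trial in multiple pregnancies that was negative overall but had a significant difference in its monochorionic subgroup. The Discussion then cites that subgroup as evidence that the pessary works.

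The same sentence also gives the primary outcome a second threshold. A final p-value between 0.045 and 0.05 would be significant under Data analysis and not significant under Expected sample size.

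**Working it through.** **1. The plan's own figures.** Inputs from Expected sample size: 40% against 26%, 80% power, two-sided test (sidedness is not stated; two-sided reproduces the plan). With mean rate 0.33:

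n per arm = [z(1−α/2)·√(2·0.33·0.67) + z(0.80)·√(0.40·0.60 + 0.26·0.74)]² / 0.14²

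- α = 0.05: (1.960·0.665 + 0.842·0.658)² / 0.0196 = 175.9, so 176.
- α = 0.045: (2.005·0.665 + 0.842·0.658)² / 0.0196 = 181.6, so 182.

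Both match the document. The 182 per arm therefore rests on testing the primary at 0.045, and the blanket 0.05 contradicts the design calculation. The documents give no family-wise figure for the secondary outcomes to reproduce.

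**2. Number of secondary tests.** Four cut-offs + four other listed outcomes + one Mantel-Cox test = 9. Maternal effects, the per-protocol analysis and the cervical-length subgroups are left out of the count.

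**3. Expected false positives if the pessary has no effect.** 9 × 0.05 = 0.45, whatever the correlation. Each single test keeps its 5% error rate.

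**4. Chance of at least one false positive among nine, either direction.**

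Independent tests: 1 − 0.95⁹ = 0.37.

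Equally correlated normal test statistics with correlation ρ and c = 1.96:

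1 − ∫ [Φ((c − √ρ·u)/√(1−ρ)) − Φ((−c − √ρ·u)/√(1−ρ))]⁹ φ(u) du

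| Assumed ρ | At least one of nine | Same, with primary not significant at 0.045 |
|---|---|---|
| 0 | 0.37 | – |
| 0.3 | 0.33 | 0.30 |
| 0.5 | 0.27 | 0.24 |
| 0.7 | 0.20 | – |
| 0.8 | 0.165 | 0.13 |

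**5. A different structure as a check.** Take only the eight listed outcomes. Draw the four cut-offs from one latent gestational age, and link the other four outcomes to it by an assumed correlation. Simulated chi-squared tests give about 0.25 to 0.32. A continuity-corrected test, standing in for Fisher's, gives about 0.21 to 0.23. Independence gives 1 − 0.95⁸ = 0.337.

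**6. The four extra cut-offs alone.** Simulated null trials, 182 per arm, 40% delivered before 32 weeks (from the document). The cumulative rates at the other cut-offs are assumptions.

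| Assumed rates at 28 / 30 / 34 / 37 weeks | Any of four, either direction | Same, with primary not significant |
|---|---|---|
| 15 / 27 / 65 / 95% | 0.165 | 0.138 |
| 20 / 30 / 60 / 90% | 0.155 | 0.125 |
| 10 / 20 / 75 / 97% | 0.168 | 0.146 |

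False benefit alone is about half of the middle column, roughly 0.08.

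**The case against.** **The outcomes are already ranked.** One primary is named, the rest are called secondary, the trial is sized on the primary alone, and the Discussion explains the choice of 32 weeks. No passage says that success may be claimed on another outcome. This stands as far as it goes: a reader might infer that the plan offers alternative routes to a positive trial, and the text does not say so. But the label does not cancel a sentence that accepts significance in every case.

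**The sentence is only a reporting threshold.** It follows directly after the software statement, and testing order is commonly left to an analysis plan. The absence of an order would be no finding by itself. The finding is the positive rule, which is worded as acceptance of significance and allows no exception.

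**The probabilities are assumptions.** This stands. The documents give no correlations and no rates for the secondary outcomes, so no single value, such as the 27% at correlation 0.5, can be presented as a property of this trial. The results also count both directions, and they are lower with Fisher-type tests.

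**Nothing happens to the primary claim.** This also stands. A reader might infer that the trial's overall 5% is inflated, or that each secondary test has an error rate several times 5%. Neither is supported. The 5% in the sample-size section belongs to the primary outcome, each test keeps its own 5%, and only the family-wise probability rises.

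**Conclusion.** The point holds as a fault in a stated rule. The sentence allows nine secondary comparisons to be declared significant at 0.05 with no control of the family-wise error, and it contradicts the 0.045 level on which the 182 per arm depends.

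If the pessary has no effect on any outcome, the chance of at least one false secondary finding in either direction is about 16.5% to 37%, for equal correlations of 0.8 down to 0 and two-sided tests. For the four extra cut-offs it is about 16%, with false benefit about 8%, given 40% before 32 weeks and assumed rates elsewhere. The conflict between 0.05 and 0.045 needs no assumption.

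The consequence is for what may be concluded from secondary results. Sample size and conduct are unaffected.

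**What to change.** Replace the blanket sentence in Data analysis with wording to this effect: statistical significance will be declared only for the primary outcome, at the final level of 0.045 given under Expected sample size. All secondary outcomes, including the other gestational-age cut-offs and the time-to-birth comparison, are supportive and will be reported as effect estimates with 95% confidence intervals and no claim of significance.

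Limiting the existing sentence to the primary without changing its number would not do, because 0.05 would then be attached to the one confirmatory test.

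If the sponsor wants a confirmatory secondary claim, a short sequence fixed in advance and tested only after a significant primary result is an option, not a requirement.

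The cost is one or two sentences, with no extra patients or data; relative risks with intervals are already planned. The price is that an isolated p < 0.05 on a secondary outcome can no longer be claimed as significant.
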